## Abstract

**Background:**

The Direct Anterior Approach (DAA) is an alternative approach to the currently most used Lateral Approach (LA) for hip replacement in femoral neck fracture patients. Compared to the LA, the DAA minimizes soft tissue damage. Sparing muscle tissue may facilitate early and improved postoperative mobility. It may also be associated with fewer complications, increased quality of life and lower 1-year mortality. The aim of this study is to compare postoperative complications, hip function and patient mobility after hemiarthroplasty via the anterior or lateral approach following a displaced femoral neck fracture.

**Methods:**

138 elderly patients with displaced femoral neck fractures will be operated using either the direct anterior approach or the lateral approach for a hemiarthroplasty in a single centre, prospective, comparative cohort study. The choice of surgical approach will depend on the expertise of the trauma surgeon on call. The primary outcome of this study will be the functionality of the hip after surgery measured using the Harris Hip Score during routine outpatient check-ups. Secondary outcomes include surgical and non-surgical complication rates, admission time, postoperative pain, rehabilitation time, performance in activities of daily living, health-related quality of life measured, cognitive function and balance.

**Discussion:**

Many approaches are known for hip replacement arthroplasty in trauma patients with little consensus on the preferred method. Identifying the best approach facilitating an adequate and fast recovery could optimize patient independence and quality of life and minimize rehabilitation costs, morbidity and mortality rates. The study design will reflect daily clinical practice and aims to present an accurate depiction of clinical outcomes.

**Trial registration:**

This trial entered the Dutch Trial Registry with registration number (NTR)6238 on the 24th of April 2017. http://www.trialregister.nl/trialreg/index.asp. Protocol version 2.0 16–03-2017.

## Background

Femoral neck fractures are amongst the most common fractures in the elderly population [1]. Treatment requires immediate hospitalization, surgical treatment and intensive physical therapy aimed at achieving prefracture levels of function and mobility [2]. Although hip arthroplasty enables early postoperative mobilization, rehabilitation is still required due to the invasive nature of the procedure and the frailty of the average patient [3]. Fast recovery is desirable as prolonged rehabilitation is associated with high morbidity and mortality rates and increased healthcare costs [4, 5].

Currently one of the most commonly used approaches for hip replacement arthroplasty is the Lateral Approach (LA), also known as the Straight Lateral, the Direct Lateral, the Hardinge or the Transgluteal Approach, which provides excellent exposure of both the proximal femur and acetabulum, but requires partial dissection of the gluteus medius muscle insertion for an adequate exposure of the capsule [6]. Consequently it is associated with postoperative abductor muscle dysfunction. This may cause a limp or Trendelenburg gait in patients with reduced abductor strength, as well as greater trochanteric pain or tenderness related to muscle injury, and dislocations of the hip [6, 7]. These adverse outcomes may be prevented by using an alternative approach, the Direct Anterior Approach (DAA), also known as the Anterior Minimal Invasive Surgery (AMIS), the Anterior Supine Intermuscular (ASI), the (modified) Smith-Petersen or the Hueter approach. The DAA is used by an increasing number of orthopaedic surgeons for (non-traumatic) Total Hip Arthroplasty (THA). Recent studies indicate that the muscle-sparing nature of this technique is beneficial to the patient’s recovery and reduces the incidence of complications [6]. Although many subtle variations of the DAA have been described, the common goal is to leave muscle tissue intact and approach the hip joint through the intermuscular spaces of the tensor fasciae latae, the sartorius, the rectus femoralis and the gluteus medius [8]. Disadvantages of the DAA include limited exposure of the hip joint which can cause difficulties in correct alignment of the femoral arthroplasty, especially in obese patients, and perioperative complications in osteoporotic bone [6]. Valgus position of the implant is a well-known pitfall of this procedure [3], as is damaging the lateral femoral cutaneous nerve [9].

Studies comparing approaches of the hip joint for THA often favour the DAA for its low dislocation rates and intact abductor function [6, 10]. Despite differences in the procedures and patient populations of THA and hemiarthroplasty (HA), a faster and better recovery with fewer complications is expected for both procedures when using a less invasive approach [10]. A few studies concerning the DAA for HA suggest benefits of the DAA over the LA, but large comparative prospective trials are lacking [11].

Sparing muscle tissue and using a less invasive approach could lead to improved postoperative mobility, less permanent institutionalization, increased quality of life, fewer complications and lower long term mortality. If clinical benefits of the DAA approach outweigh its disadvantages, this approach could be preferable over the LA for HA after displaced hip fractures.

### Objective

The aim of this study is to compare hip function, postoperative complications and patient mobility after hemiarthroplasty via the anterior or lateral approach for a displaced femoral neck fracture in elderly patients.

## Method/design

This single centre prospective comparative cohort study is part of the ‘Hip Fracture Centre’ (HFC) project that prospectively documents the treatment outcomes of all consecutive hip fracture patients admitted to the Haaglanden Medical Centre (HMC) Bronovo in The Hague, the Netherlands. The HMC annually treats more than 500 patients with proximal femoral fractures and is part of a major trauma centre collaboration in the western part of the Netherlands. The HFC project is a multidisciplinary project designed to improve the care for hip fracture patients in our hospital.

### Study population

All consecutive patients 70 years or older admitted to the study hospital with an X-ray proven displaced femoral neck fracture (AO type 31 B1-B3), treated with a cemented hemiarthroplasty who are considered able to rehabilitate will be included in this study. Eligibility for rehabilitation is determined during hospitalization for all patients in twice weekly assessments by a multidisciplinary team, including a trauma surgeon, ward doctor, trauma nurse, physiotherapist, dietician, geriatrician and a transfer nurse. Patients are considered fit for rehabilitation when they can participate in physiotherapy by being physically and mentally able to adequately follow instructions. Patients fit for rehabilitation are either discharged home with ambulatory physiotherapy, or to a geriatric rehabilitation care institute. Patients with an active lifestyle and unrestricted mobilization without walking aids are considered eligible for total hip arthroplasty by the treating trauma surgeon and are excluded from the study. Inclusion and exclusion criteria are presented in Table 1.

**Table 1 Tab1:** Inclusion and exclusion criteria for eligible study subjects

Inclusion criteria	Exclusion criteria
Age ≥ 70 years	Eligible for total hip arthroplasty^a^
X-ray proven displaced femoral neck	Treated with an uncemented hemiarthroplasty
Fracture (AO type 31 B1-B3)	Incapable of rehabilitation due to severe cognitive impairment
Able to rehabilitate	Incapable of rehabilitation due to pre-existing physical restrictions.
	Concomitant traumatic comorbidities restricting long-term rehabilitation.

^a^Patients with an active lifestyle and unrestricted mobilization without walking aids

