#### Surgical procedures

Surgery will be performed by experienced surgeons in accordance with the national surgical treatment protocol for proximal femoral fracture of the Nederlandse Vereniging voor Heelkunde (Dutch trauma surgery society). The choice of a specific surgical approach will depend on the experience of the surgeon on call: all surgeons use the approach they are most familiar with. The group consists of 16 highly experienced orthopaedic trauma surgeons. Residents with insufficient experience to perform the operation independently, operate under strict supervision of the trauma surgeons. The LA and DAA are standard approaches for hemiarthroplasty in the study hospital.

Patients are operated as soon as possible after full medical check-up (including laboratory tests, physical examination and consultation by a geriatric specialist) and anaesthesiological approval.

The prosthesis used will be the self-centring, 3-point-contact anchorage cemented CCA straight stem prosthesis in accordance with [name] in a standard of lateral version combined with a short or medium hemiprosthesis head produced by of Mathys Medical®. Patients with a severe history of cardiovascular diseases with pump failure or hypotension during operation are at risk of adverse events associated with bone cement implantation syndrome and are excluded from the study and treated with an uncemented prosthesis. This is assessed and decided subjectively by the treating anaesthesiologist and trauma surgeon.

The anterior approach will be performed with the patient in a supine position. An incision of about 15 cm is made in a straight line starting two fingers lateral and caudal of the spina iliaca anterior superior heading towards the lateral side of the patella. The fascia is dissected between the m. tensor fascia lata and the m. sartorius. Using blunt dissection of the intermuscular space, the crossing vessels are cauterized and dissected. The capsule is excised to expose the joint. After completion of the procedure, the wound is closed in layers.

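### The surgeon judges the THA exclusion on a partly unmeasured criterion and also determines the approach, so the fittest patients can leave the DAA and LA cohorts at different rates

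*Protocol article*

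**What the plan says.** **Exclusion.** The Study population section and the footnote to Table 1 describe the patients to be left out: "Patients with an active lifestyle and unrestricted mobilization without walking aids". The section says that they "are considered eligible for total hip arthroplasty by the treating trauma surgeon and are excluded from the study". It gives no scale or cut-off for an active lifestyle.

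**Exposure.** The abstract (Methods) states: "The choice of surgical approach will depend on the expertise of the trauma surgeon on call". Surgical procedures adds that "all surgeons use the approach they are most familiar with" and that "The group consists of 16 highly experienced orthopaedic trauma surgeons". How the 16 divide between DAA and LA is not stated.

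**Who decides other entry criteria.** Fitness to rehabilitate goes to a team: "Eligibility for rehabilitation is determined during hospitalization for all patients in twice weekly assessments by a multidisciplinary team". THA eligibility does not. The exclusion for an uncemented prosthesis is also partly the surgeon's: "This is assessed and decided subjectively by the treating anaesthesiologist and trauma surgeon".

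**Adjustment.** Statistical analysis plans a propensity score built from the available baseline parameters. Baseline parameters lists, among others, age, ASA class, BMI, 6CIT, and prefracture Katz ADL and EQ-5D. Walking-aid use, activity level and prefracture HHS are not listed.

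**Denominator.** Under Method/design, the Hip Fracture Centre (HFC) project "prospectively documents the treatment outcomes of all consecutive hip fracture patients".

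**The concern.** A non-randomised comparison needs entry to be unrelated to exposure, at least given the covariates that are adjusted for. Here a surgeon's judgement decides whether a fit patient is a THA candidate and so leaves the study, and the surgeon also determines the approach. If surgeons who use one approach set a lower threshold for THA, their cohort loses more of its fittest patients. That cohort would then tend to look worse on the HHS, and on SPPB, TUG and Katz ADL, even if the two approaches were equivalent.

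With only 16 surgeons split between two approaches, individual thresholds need not average out, even if nothing links approach and threshold systematically. The propensity score is fitted to patients who remain after the exclusion, and it lacks the variables that define the exclusion. It can therefore balance the cohorts on prefracture mobility only through proxies such as Katz ADL and EQ-5D.

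**Working it through.** **1. Inputs from the Sample size section.** Target difference 10 HHS points, SD 15, 41 evaluable patients per cohort, 40% loss to follow-up. The inflation reproduces: 41/(1 − 0.40) = 68.3, so 69 per group and 138 in total. The 41 does not follow from the usual two-sided formula: 2 × (15 × (1.960 + 0.842)/10)² = 35.3, so 36, or 37 by the t-test. With 41 per group the power is about 85%. That discrepancy is conservative and does not bear on this point. The 41 is used below only for the standard error: 15 × √(2/41) = 3.31.

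**2. Assumptions.** The article gives no THA rates by surgeon or approach. Suppose that THA patients come from the top fraction p of a normal prefracture-fitness scale, and that fitness correlates r = 0.5 (range 0.3 to 0.7) with 12-month HHS.

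**3. Unadjusted bias.** The mean of a standard normal truncated above at its (1 − p) quantile z is −φ(z)/(1 − p).

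- p = 0.20: −0.2800/0.80 = −0.350
- p = 0.05: −0.1031/0.95 = −0.109
- Difference 0.241 SD; bias = 0.241 × 15 × 0.5 = 1.8 points

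| THA rates in the two surgeon groups | Bias at r = 0.5 | Range, r = 0.3 to 0.7 |
|---|---|---|
| 20% and 5% | 1.8 | 1.1 to 2.5 |
| 30% and 10% | 2.3 | 1.4 to 3.2 |
| 15% and 10% | 0.6 | 0.4 to 0.8 |
| equal | 0 | 0 |

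**4. Effect on the test.** With bias b, two-sided rejection under no true effect is 1 − Φ(1.96 − b/3.31) + Φ(−1.96 − b/3.31). This gives 8.4% at b = 1.8 and 11.7% at b = 2.5, instead of 5%.

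**5. After adjustment.** The 20% and 5% case at r = 0.5 was simulated, with linear adjustment for a baseline measure whose correlation with fitness was varied (assumed values):

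| Correlation of the measure with fitness | Remaining bias (points) |
|---|---|
| none | 1.8 |
| 0.5 | 1.5 |
| 0.7 | 1.1 |
| 0.8 | 0.8 |
| 1 (fitness itself) | 0 |

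At 1.1 points the error rate is about 6%.

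**6. Cross-check with a two-group model.** A share f of otherwise eligible patients meets the THA description and scores D points higher, and a fraction e of them is excluded. The share left is f(1 − e)/(1 − fe). With f = 0.3, D = 15 and e = 0.9 or 0.5, the shares are 0.03/0.73 = 0.041 and 0.15/0.85 = 0.176, so the bias is 15 × 0.135 = 2.0 points. Over f = 0.2 to 0.4, D = 10 to 20, and e of 0.9 to 1.0 in one group and 0.5 to 0.7 in the other, the unadjusted bias runs from about 0.5 to 5.0 points. The top of that range needs one group to retain half of the patients who meet the exclusion criterion.

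**The case against.** The strongest case against is that this is ordinary residual confounding in a study openly declared non-randomised, with adjustment already planned. Much of that stands.

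- **A common criterion exists.** All surgeons work in one hospital under one national guideline, and walking without aids is a fairly concrete condition. A reader might picture a patient who uses a stick outdoors being given a THA by one surgeon and a hemiarthroplasty by another. As written, that patient does not meet the criterion and stays in either cohort. The discretion lies mainly in the unmeasured active lifestyle.
- **No evidence of differing thresholds.** A reader might infer from the Background that DAA surgeons perform more THAs. That remark concerns non-traumatic THA by orthopaedic surgeons and says nothing about thresholds in fracture patients.
- **One link is inferred.** The exclusion is assigned to the treating surgeon and the approach to the surgeon on call. That they are the same person is a reasonable reading, not a statement.
- **Adjustment can work.** It might be thought that no baseline adjustment can help because the excluded patients are gone. That is wrong: conditioning on the fitness that drives exclusion removes the bias among those who remain, as step 5 shows. The difficulty is only that the defining variables are not on the list.
- **The article is condensed.** The full protocol may define eligibility in more detail. But the article does state who decides, on what description, and which baseline parameters are collected; the point rests on those statements.

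**Conclusion.** The point holds as a structural weakness. Entry can depend on both the approach and prefracture fitness, because a surgeon's judgement governs the THA exclusion, the approach follows the surgeon, and the variables that define the exclusion are missing from the listed adjustment set. It would be too strong to say that the cohorts are selected differently, or that DAA is favoured or penalised: the article gives no exclusion rates and no direction.

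The likely size is modest. At assumed THA rates of 20% and 5% and a correlation of 0.5, the bias is about 1.8 HHS points unadjusted and 0.8 to 1.5 with a partial proxy, against a 10-point target. It is zero if the rates are equal. A bias of this size would not create a 10-point effect, but it is avoidable and, as the article stands, unchecked. The change should be made.

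**What to change.** 1. **Record the items independently.** The emergency department and ward staff who already register baseline data would record prefracture walking-aid use, unrestricted mobilisation and activity level at admission, on a simple fixed scale.
2. **Apply the exclusion uniformly.** The Table 1 footnote exclusion would be taken from that record for every patient, whatever implant is given.
3. **Extend the propensity score.** Add prefracture mobility and walking-aid use to the baseline parameters that feed it.
4. **Report the selection.** From the HFC register, tabulate the number and baseline characteristics of THA-treated patients by the usual approach of the surgeon on call. Surgeon identity is not among the listed parameters, so record it, or the usual approach, if it is not already held.
5. **Sensitivity analysis.** If the proportions differ, repeat the HHS comparison within the range of prefracture function that both surgeon groups cover.

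The cost is one to three admission items, revised eligibility wording, one table, the loss of a few active hemiarthroplasty patients, and lower precision in the restricted analysis. Patients given a THA still leave a hemiarthroplasty cohort, so the surgeon's influence is reduced and made visible, not eliminated. The change concerns study eligibility and analysis only; treatment does not change.

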### Outcomes

#### Primary outcome

The primary outcome of this study is the assessment of daily life functionality of the hip fracture patient after cemented hemiarthroplasty using the Harris Hip Score (HHS).

#### Secondary outcomes

##### Clinical outcomes

Surgical parameters: mean operation time (skin-to-skin), mean total blood loss.Surgical complication rates (postoperative bleeding,^1^ haematoma formation, implant failure, implant dislocation,^2^ implant luxation, femoral head necrosis, periprosthetic fractures,^3^ superficial wound infection,^4^ deep wound (prosthesis) infection,^5^ nerve damage^6^).Cognitive status measured with the 6CIT score [12, 13] at admission to the hospital and at 6 weeks, 3 months and 12 months after surgery, and DOS scores during admission [14].Duration of hospital stay, cause of delayed discharge (considered later than 72 h after surgery), discharge destination and duration of rehabilitation (in days).Readmission and operative revision rate.1-year mortality.^7^
Non-surgical complications up to 12 months after surgery (delirium,^8^ anaemia,^9^ cardiac complications (decompensation and ischemia), CVA, pressure sores,^10^ electrolyte disturbances, pulmonary embolism,^11^ pneumonia,^12^ renal failure, sepsis,^13^ deep venous thrombosis^14^ and urinary tract infections^15^).Functionality and balance through a series of physiotherapeutic tests (Short Physical Performance Battery [15], Timed Up and Go test [16], Functional Ambulatory Categories [17]) at 6 weeks, 3 months and 12 months after surgery.Pain measured using a visual analogue scale (VAS) during in-hospital treatment and at 6 weeks, 3 months and 12 months after surgery.Patient-reported performance in activities of daily living using the Katz ADL Index [18] at 6 weeks, 3 months and 12 months after surgery.Health-related quality of life using the EQ-5D questionnaire [19, 20] at 6 weeks, 3 months and 12 months after surgery.

### Baseline parameters

Additional parameters include: age, sex, date of birth, general health score (using the ASA classification [21]), fracture type and side, date and time of admission and surgery, surgeon’s experience level, type of anaesthesia, surgical approach, Body Mass Index, preoperative cognition state (using the 6CIT score), preoperative nutritional state (using the SNAQ [22]) and use of osteoporosis medication. The prefracture performance in activities of daily living (using the Katz ADL) and health-related quality of life (using the EQ-5D) before the fracture will be assessed during admission as a baseline measure.

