### Treatment and procedures

Patients admitted to the hospital with a proximal femoral fracture will be treated according to the treatment guidelines for proximal femoral fracture in the elderly of the Nederlandse Vereniging voor Heelkunde (Dutch trauma surgery society) [23]. A timeline with all scheduled data registrations and assessments is presented in Table 2
*.*

**Table 2 Tab2:** Timeline for scheduled procedures and assessments

Procedure/Assessment	Admission	In-hospital treatment phase	6 weeks after surgery^a^	3 months after surgery^a^	12 months after surgery^a^
*Baseline measurements*	X				
*Physical examination*	X	X	X	X	X
*X-ray assessment*	X				
*Katz ADL*	X		X	X	X
*EQ-5D*	X		X	X	X
*6CIT*	X		X	X	X
*SNAQ*	X				
*VAS pain*		X	X	X	X
*Complication* ^*a*^ *registration*		X	X	X	X
*Mobility tests* ^*b*^			X	X	X

^a^Any patient reported complication in the previously described surgical and non-surgical complication list and any reason for a postoperative readmission to a hospital

^b^HHS, SPPB, TUG, FAC

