### Statistical analysis

Demographic and clinical characteristics of the cohorts will be described using summary statistics and will be compared by univariate analysis. Categorical variables will be compared using the chi-squared test if the data are sufficiently large (expected cell counts >5) or the Fisher’s exact test if this requirement cannot be met. Continuous variables will be compared by unpaired t-tests for normally distributed data, and by the Wilcoxon rank sum test for not normally distributed data.

Outcome parameters will be compared univariably between cohorts, but correction for confounding factors is of major importance because the patients in this study are not randomized. Since the number of study participants is limited relative to the number of potential confounders, a propensity score will be calculated from the available baseline parameters. The propensity score will be used to adjust for differences between the two cohorts in multivariable linear regression analyses for continuous outcome parameters and in multivariable logistic regression analyses for binary outcomes. Repeated outcome measures such as the HHS and pain score will also be analysed using Generalized Linear Models. *P*-values <0.05 will be considered statistically significant. All statistical analyses will be performed using IBM SPSS Statistics version 20.0 or higher.

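### No prefracture walking ability is named at baseline, so the propensity score can adjust the HHS and mobility outcomes for prefracture function only through Katz ADL and EQ-5D

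*Protocol article*

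**What the plan says.** **Outcomes.** The primary outcome is the Harris Hip Score after surgery. The SPPB, TUG and FAC are secondary outcomes at 6 weeks, 3 months and 12 months.

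**Baseline.** The Baseline parameters section lists age, sex, ASA class, fracture details, timing, surgeon's experience, anaesthesia, approach, BMI and 6CIT, ending with "preoperative nutritional state (using the SNAQ [22]) and use of osteoporosis medication". It then adds that Katz ADL and EQ-5D status "before the fracture will be assessed during admission as a baseline measure". No walking-aid, ambulation or hip item appears.

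**Schedule.** Treatment and procedures introduces Table 2 with the words "A timeline with all scheduled data registrations and assessments is presented in Table 2". The mobility row, footnoted as "HHS, SPPB, TUG, FAC", is marked only at the three postoperative visits. Katz ADL, EQ-5D and 6CIT are marked at admission as well.

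**Eligibility and allocation.** The footnote to Table 1 describes those eligible for total hip arthroplasty, who are excluded: "Patients with an active lifestyle and unrestricted mobilization without walking aids". Study population leaves this judgement to the treating trauma surgeon. Under Surgical procedures, the approach depends on the experience of the surgeon on call.

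**Adjustment.** Statistical analysis calls correction for confounding of major importance and says that the propensity score is "calculated from the available baseline parameters".

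**The concern.** The trial compares hip function and mobility between two groups that were not randomised, and it relies on a propensity score to make them comparable. The score can balance only what was recorded. For two secondary outcomes, Katz ADL and EQ-5D, the plan takes a prefracture value of the same instrument. For the primary outcome and the mobility tests it takes nothing from the same domain.

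How well a patient walked before the fracture plausibly predicts how well that patient walks a year later. The Background itself describes treatment as aiming at the prefracture level of function and mobility. If the two cohorts differ in prefracture walking ability in a way that Katz ADL, EQ-5D, age, ASA class and the other listed items do not capture, part of that difference would be read as an effect of the approach. An analysis plan cannot repair this later if the variable was never collected.

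**Working it through.** **1. What is available for adjustment.** Set side by side:

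| Measure | Before the fracture (recalled) | After surgery |
|---|---|---|
| Katz ADL | yes | 6 weeks, 3 and 12 months |
| EQ-5D | yes | 6 weeks, 3 and 12 months |
| HHS (primary) | no | 6 weeks, 3 and 12 months |
| SPPB, TUG, FAC | no | 6 weeks, 3 and 12 months |
| Walking-aid use | judged within an eligibility criterion, not listed as recorded | not listed |

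Prefracture function therefore reaches the propensity score only through Katz ADL and EQ-5D.

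**2. Is there a route from mobility to approach?** Study population has the treating surgeon judge total-hip eligibility, partly on unaided walking. Surgical procedures ties the approach to the surgeon on call. If the same surgeon makes both decisions, and surgeons differ in where they draw the total-hip line, the mobility range admitted to each cohort can differ. This is a possible mechanism. The protocol gives no data on whether it operates or in which direction.

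**3. Is a recalled item feasible?** Preoperative procedures has a nurse register the baseline questionnaires, including Katz ADL and EQ-5D, on the ward before surgery. One more recalled question fits that step. An HHS examination, SPPB or TUG cannot be done on a freshly fractured hip, and none is asked for here.

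**4. The plan's own figures.** Sample size gives a target difference of 10 HHS points, SD 15, α = 0.05 and power 80%. Taken as two-sided:

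- n per group = 2 × (1.960 + 0.842)² × 15² / 10² = 35.3, so 36 (37 with the t-test). The stated 41 is larger and gives about 85% power.
- 41 / (1 − 0.40) = 68.3, so 69 per group and 138 in total, as stated.

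Only the 10 points and the SD of 15 are used below. The point does not depend on the 41.

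**5. Illustrative size.** Let r be the partial correlation of prefracture mobility with 12-month HHS given the other covariates, s the residual SD of the HHS after those covariates, and d the systematic imbalance in mobility left after them, in SD units. Then

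shift = r × s × d.

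Both r = 0.3 to 0.6 and d = 0.3 are assumptions; the documents give neither. The residual SD cannot exceed the total SD, so s = 15 gives the upper limit:

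- r = 0.3: 0.3 × 15 × 0.3 = 1.35 points, or 13.5% of 10
- r = 0.6: 0.6 × 15 × 0.3 = 2.70 points, or 27% of 10

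If the recorded covariates together had a multiple correlation of 0.5 with the HHS (also an assumption), s = 15 × √(1 − 0.25) = 13.0, and the shifts fall to 0.3 × 13.0 × 0.3 = 1.17 and 0.6 × 13.0 × 0.3 = 2.34 points. With d = 0 the shift is zero.

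**The case against.** **The list may not be complete.** The article introduces its baseline items as parameters that are included, Table 2 has an unitemised row for baseline measurements, and the study sits inside a wider hip fracture registration. A mobility item could be in the full protocol. This stands as a caution: if such an item is already collected, the change reduces to naming it in the adjustment. However, Table 2 is introduced as covering all scheduled registrations, and nothing in the article points to a mobility item at admission.

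**Prefracture function is partly covered.** This also stands. Katz ADL and EQ-5D can enter the score with age, ASA class, 6CIT, BMI and SNAQ. What is missing is a direct measure of walking, not all information on function.

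**Confounding is not shown.** A reader might infer that prefracture mobility is the strongest confounder here. The documents do not support that. Approach follows the surgeon on call, no passage says that patient mobility steers it, and the exclusions narrow the mobility range at both ends. Its prognostic role is plausible, and its association with approach is only possible.

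**Chance imbalance is not bias.** A reader might also count an accidental difference between cohorts as bias. It is random error, already reflected in the standard error. The illustration therefore applies only to a systematic imbalance.

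**Walking-aid status need not be on file.** The total-hip criterion is a composite. A patient without an active lifestyle fails it whatever the walking-aid use, so the criterion does not prove that the item was established for everyone.

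**Conclusion.** The point holds as a worthwhile, inexpensive improvement. As described in the article, the plan leaves the domain of its primary outcome adjusted only through general proxies, in a design that itself calls confounding control of major importance.

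The size is unknown. Under the stated assumptions (a systematic imbalance of 0.3 SD left after the other covariates, and a partial correlation of 0.3 to 0.6) the HHS comparison would shift by at most about 1.4 to 2.7 points, and by less once the residual SD is below 15. The direction cannot be given.

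No gain in power is claimed. A reader might compute one by setting an adjusted analysis against a plain t-test. The plan already intends an adjusted analysis, so that is the wrong starting point, and 41 per group already exceeds 80% power on the plan's own inputs. Some gain in precision is likely, but the documents do not allow it to be sized.

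**What to change.** - Add one recalled prefracture mobility item, either walking-aid use or an FAC category, to the questionnaires that the nurse registers before surgery, and show it in the admission column of Table 2.
- For patients already entered, complete it from the files where the information exists, and report how many values remain missing.
- Name the item in the propensity score, and include it as a covariate in the HHS, SPPB, TUG and FAC models. The score addresses imbalance between cohorts; the direct covariate also uses the item's prognostic value.
- Report its distribution by cohort, so that readers can see whether the groups differed.

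The cost is one question on an existing form and a file review. The item carries recall error, as the Katz ADL and EQ-5D baselines already do, and it may be missing for some patients entered before the change.
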